## Abstract

**Background:**

Among patients with rectal cancer, 5–10 % have a primary rectal cancer beyond the total mesorectal excision plane (PRC-bTME) and 10 % recur locally following primary surgery (LRRC). In both cases, patients ‘care remains challenging with a significant worldwide variation in practice regarding overall management and criteria for operative intervention. These variations in practice can be explained by structural and organizational differences, as well as cultural dissimilarities. However, surgical resection of PRC-bTME and LRRC provides the best chance of long-term survival after complete resection (R0). With regards to the organization of the healthcare system and the operative criteria for these patients, France and Australia seem to be highly different. A benchmarking-type analysis between French and Australian clinical practice, with regards to the care and management of PRC-bTME and LRRC, would allow understanding of patients’ care and management structures as well as individual and collective mechanisms of operative decision-making in order to ensure equitable practice and improve survival for these patients.

**Methods/design:**

The current study is an international Benchmarking trial comparing two cohorts of 120 consecutive patients with non-metastatic PRC-bTME and LRRC. Patients with curative and palliative treatment intent are included. The study design has three main parts: (1) French and Australian cohorts including clinical, radiological and surgical data, quality of life (MOS SF36, FACT-C) and distress level (Distress thermometer) at the inclusion, 6 and 12 months; (2) experimental analyses consisting of a blinded inter-country reading of pelvic MRI to assess operatory decisions; (3) qualitative analyses based on MDT meeting observation, semi-structured interviews and focus groups of health professional attendees and conducted by a research psychologist in both countries using the same guides. The primary endpoint will be the clinical resection rate. Secondary end points will be concordance rate between French and Australian operative decisions based on the inter-country reading MRI, post-operative mortality and morbidity rates, oncological outcomes based on resection status and one-year overall and disease-free survival, patients’ quality of life and distress level. Qualitative analysis will compare obstacles and facilitators of operative decision-making between both countries.

**Discussion:**

Benchmarking can be defined as a comparison and learning process which will allow, in the context of PRC-bTME and LRRC, to understand and to share the whole process management of these patientsbetween Farnce and Australia.

**Trial registration:**

NCT02551471. (date of registration: 09/14/2015)

## Background

Over the last two decades, oncological outcomes for primary rectal cancer have improved due to refinements in neoadjuvant radiotherapy, chemotherapy and surgery. However, difficulties in resectability of the rectum come from its anatomical location and its close link to the pelvic skeleton, the lateral pelvic nerves and vessels, and the genitourinary system. These anatomical limits can affect the resectability of primary rectal cancer beyond the total mesorectal plane (PRC-bTME) and locally recurrent rectal cancer (LRRC). In fact, 5 to 10 % of cases of rectal cancer are bTME at the time of diagnosis with an extension to an adjacent organ (T4bNxM0) limiting their resectability [1, 2]. After radiochemotherapy, 30 % of these tumours will be resectable at the cost of extensive pelvic surgery and 10 % remain non-resectable [3]. Among patients operated for curative purposes (R0) for rectal cancer, 5 to 10 % will present LRRC within 5 years [4, 5] with a wide range of resectability rates between countries and institutions [6–10]. Nevertheless, surgery for curative purposes constitutes the “cornerstone” of the care and management of rectal cancer [11] for PRC-bTME [12–14] and LRRC [15–17], requiring multi-visceral resections associated with postoperative morbidity and mortality rates of 60 and 2 %, respectively [18]. The care and management of PRC-bTME and LRRC represents decisional conflict of the subjective and objective benefits and risks of the curative and palliative treatment options.

### The current state of knowledge

#### PRC-bTME

The 7th edition of the American Joint Committee on Cancer’s (AJCC) TNM - staging system (2010) [19] subdivided the T4 stage of rectal tumours in two sub-stages: stage T4a, in which the tumour has grown into the visceral peritoneum, and stage T4b in which the tumour is referred to as “fixed” or bTME and associated with a decrease in 5-year overall survival [20, 21]. In spite of a more pejorative prognosis of T4b tumours, extended multi-visceral surgical resection with a R0 margin allows 5-year survival identical to that of T3 or T4a tumours, at the cost of a higher post-operative morbidity rate [12, 13]. The resection rate of 35 % for PRC-bTME has been only reported in an Australian government report [22] regarding PRC-bTME and LRRC. No scientific publication has reported this to our knowledge.

#### LRRC

The rate of pelvic recurrence after rectal surgery for curative purposes has vastly diminished since the utilisation of pre-operatory radiotherapy [23] and the development of total mesorectal excision (TME) [11], varying from 5 to 10 % at 5 years [4, 5]. In half of the cases, recurrence is isolated in the pelvis. The resection rate for curative purposes (R0) of these pelvic recurrences varies in the literature from 22 to 74 % [24] and in a third of cases, excision is extended to adjoining organs (sacrum, uterus, vagina, prostate, bladder) [6] allowing to achieve a median survival from 19 to 31 months [6–10] and a 5-years overall survival of 40 % [25]. In the absence of surgical excision, the survival rate is lower than 4 % at 5 years with a median survival rate of 3.5 at 13 months [17]. The utilisation of radiotherapy or chemotherapy on their own only allows an improvement of the symptoms, without modifying survival. Several classifications aiming to predict resectability of this recurrence have been published taking into account: the symptoms [6], the site and degree of fixation [6, 26], the depth of colorectal-wall invasion and adjacent organs [27], the anatomical region of the pelvis invaded by the recurrence [28] and the dissection plans defined by the MRI after neoadjuvant treatment [29]. The resection rate of 42 % for LRRC has been only reported in an Australian government report [22] regarding PRC-bTME and LRRC. No scientific publication has reported this to our knowledge.

### Hypotheses of the research

This research project rests on the comparison between two countries that appear to contrast with regards to the care management of PRC-bTME and LRRC, France and Australia. Regarding its healthcare system for patients with PRC-bTME and LRRC, Australia equipped itself with a veritable policy of centralisation and clinical pathway, appearing as a national and international referral country in this surgical field [22]. On the other hand, France and other European countries [30] do not have this clinical pathway policy for patients with PRC-bTME and LRRC which may have resulted in high variability and heterogeneity of management for these patients.

The main hypotheses of research are that these differences rest on individual and collective representation of disease, organisations, structures, clinical pathway and care management. The understanding of this whole process will allow an optimisation of surgical indications and an improvement in patients’ survival. Benchmarking of clinical practices is the process of a structured comparison and the sharing of good practices of clinical care; it is based on a quality of care assessment and allows for continuous improvement of this quality of care.

In this context, a benchmarking-type analysis of surgical indications between France and Australia, but also the differences between organisations, care management systems for patients as well as in individual and collective mechanisms (representations, reasons, patterns) linked to surgical decision-making will allow a better understanding of these differences in practice and, over time, their homogenisation in order to improve care in both systems.

## Aims

The main objective of our study is to evaluate and compare, in a prospective benchmarking study, the operative-decision making and practice for PRC-bTME and LRRC in France and Australia.

Secondary objectives include assessment of concordance of operative-decisions made in MDT meetings, quality of surgery, post-operatory morbidity and mortality, disease-free survival, and overall survival, the quality of life and distress level of patients, the individual and collective mechanisms of decision-making and the structural and organisational contexts of care management between France and Australia.

## Methods and design

### Ethics statement

This non-interventional study has been approved by French and Australian national Institutional Review Boards: the Regional Comity of Patients Protection of South-West III (France), N°DC2015/22; and by the Sydney Local Health District Ethics Committee (Australia): HREC/15/RPAH/83&X15-0056; HREC/15/RPAH/123&X15-0091 and HREC/15/RPAH/208 &X15-0149. This study is supported by a grant from the French Ministry of Health (PREPS-14-0070). The institutional promoter is the Bordeaux University Hospital (DRCI: Direction de la Recherche Clinique et de l’Innovation).

### Consent statement

Before inclusion into this prospective study, all patients will sign consent for participation. As this trial is a non-interventional study, this consent will inform the patient about details regarding the study protocol, eligible criteria and objectives of the research.

### Population and design

The study protocol was conceived following an international benchmarking-type pilot study, allowing for the most rigorous assessment of the whole care management processes for patients with PRC-bTME and LRRC in France and Australia. Patients are included from 10 French and 2 Australian tertiary colorectal centres (see list of participating centers in the Acknowledgments section). Approval from all participating centers has been obtained. The study design includes three parts:French and Australian national cohortsAll patients must fulfil the following criteria: PRC-bTME or LRRC without distant metastases for curative, i.e. surgical resection, or palliative, i.e. no surgical resection, treatment intent. The complete inclusion and exclusion criteria are given in Table 1. This is a non-interventional study, no supplementary examinations to those performed in the framework of patient care management will be carried out for the inclusion of patients. According to the guidelines established by a consensus of international experts [1], before inclusion, the patients should have a pelvic MRI and a thoracoabdominal-pelvic scan. Patients should be included after MDT meeting discussion, irrespective of a curative or palliative treatment decision. Patients not included in the study, due to exclusion criteria, will be captured for calculation of incidence.

**Table 1 Tab1:** Inclusion and exclusion criteria

Inclusion criteria	Exclusion criteria
• Primary rectal cancer (ymrT4bNxM0) or Local rectal recurrence cancer without distant metastases after partial or total mesorectal excision • Patient’s health condition which enable surgical • procedure and/or radiotherapy and/or chemotherapy • Age ≥18 years old • Oral agreement after reading information letter • Patient who benefits by medicare system	• Primary rectal cancer status lower than ymrT4b • Primary rectal cancer or Local recurrence rectal cancer with distant metastases • Patient’s health condition which don’t enable surgical procedure and/or radiotherapy and/or chemotherapy • Pregnancy or breast feeding period • Patient into the care of a guardian • Patient under the protection of the Court • Inability to give oral agreement due to bad comprehension capacity • Inability to be followed by medical team for geographic, social or psychologic reasonsThe data collected, in France as well as in Australia through a Clinical Report Form (CRF), will include clinical data, radiological data, (neo) adjuvant therapies, surgical and pathological data, quality of life and distress level. At inclusion, 6 and 12 months, the evaluation of quality of life and distress level will be collected using validated self-reported questionnaires, the MOS SF36 [31], FACT-C [32] and the Distress Thermometer [33], respectively.Patients will be followed in clinics according to he habits of each department. Usual follow-up is composed of clinical exam, CEA analysis, CT-scan or Chest Radiography with abdominal ultra-sound every 3–4months during the first three years and every 6 months for the last two years.Blinded inter-country reading of pelvic MRIThis experiment will consist of an inter-country reading of patients’ pelvic MRIs, “blind” to the other country’s decision. All centres will use the same MRI protocol with an uniform report. The MRI shared will be the one based on which the curative (surgery) or palliative care management decision (no surgery) the treatment decision will be made, that is to say, the MRI done after possible neoadjuvant treatment. Pelvic MRIs will be transferred after anonymization (Dicom Cleaner software®). In the case of medical contraindication to undergo pelvic MRI, the appropriate diagnostic scan will be used to assess the care-decision concordance between both countries.Qualitative analysisQualitative data will be collected by a research psychologist, based on MDT meeting observation, semi-structured interviews and focus groups of practitioners (surgeon, oncologist and radiologist) involved with the therapeutic decisions of patients with PRC-bTME and LRRC. The procedure of qualitative investigation will be carried out in an identical manner in France and Australia and will rest on the following methodological plan:MDT meeting observation (3 per centre) with “real” patient cases and “theoretical” patient cases (blinded pelvic MRI re-reading). This will be made in reference to the recommendations decreed by Mucchielli [34] and Norimatsu & Pigem [35]: a researcher in psychology will attend MDT meeting (“real” and “theoretical”) with the help of an observation guide previously established.Semi-structured exploratory interviews and focus group will be conducted with MDT health professional attendees (oncologists, radiologists and surgeons) to identify care management systems for PRC-bTME and LRRC patients, explore social representations that direct the formulation of a therapeutic decisions and identify cultural, medical and personal factors. Both semi-structured interviews and focus groups will be carried out using an interview guide with open questions and in the broadest sense possible in order to avoid any phenomena of induction [36]. Techniques such as word association, reminders and reformulations will be used during the interviews and focus groups.

A flowchart is given in Fig. 1.

**Fig. 1 Fig1:**
[figure not shown]
Flow chart PelviCare trial

### Endpoints

#### Primary endpoint

The primary end point of the study is the clinical resection rates in both countries. It will be expressed as a percentage and corresponding to the ratio between the number of patients operated and the number of patients discussed in colorectal MDT meetings for PRC-bTME and LRRC. These rates will be expressed separately in each country and compared.

#### Secondary endpoints

Secondary end points of the study are:The concordance rate of operative decisions between France and Australia. An analysis of concordance between French and Australian operative decisions will be carried out through the radiological (or theoretical) resectability rate, expressed as a percentage and corresponding, after blind inter-country reading of pelvic MRIs, to the ratio between the number of patients judged to have resectable tumours and the number of all MRI re-reading.The post-operative morbidity and mortality rates within 30 postoperative days for patients with curative treatment intent will be evaluated according to the Dindo classification [37].The oncological outcomes, based on the R0 resection rate and the 1-year overall survival and disease-free survival.The comparison of quality of life, according to MOS SF-36 and FACT-C questionnaires.The comparison of the distress level of patients according to the distress thermomether scale.

Qualitative analyses have its own end points with regards to verbal and non-verbal elements during therapeutic decisions: spatial positioning of the participants, speaking and division of speaking time, denouement of the exchanges (temporal dynamic), argument and counter-arguments, silences, overlapping of words, distribution of speaking time, leader effect, et al. identification of individual (intra-personal level), collective (inter-individual level) and contextual (institutional and socio-cultural level) obstacles and facilitators of operative decision-making.

### Statistical considerations

#### Caculation of the size of the population

The principal objective is to compare care management practices for patients suffering from PRC-bTME and LRRC, between France and Australia. The primary end point is the clinical resection rate. We make the hypothesis that in France the clinical resection rate will be 20 % and that in Australia it will be 40 %. In this situation, the calculation based on the formula of Yates’ chi-squared test with a risk α of 5 % and a power 1-β of 90 %, it must include at least 120 patients in each country, for a total of 240 patients (nQuery Advisor 7.0®).

One of the secondary end points of the study consists in the analysis of concordance between French surgical decisions and Australian ones (more specifically regarding the indication to resectability). We expect the concordance of the indication to resectability between France and Australia to be moderate. Kappa coefficient of 0.6, and show that this is different from 0.4 with a power of 80 % and an alpha risk of 5 %. The necessary number of patients to include is 240.

#### Statistical analysis

The data will be analysed by the biostatistician of the Methodology and Data Management Centre (Centre de Méthodologie et de Gestion des données – USMR). The analyses will be carried out with SAS® software (version 9.2 and later versions). The quantitative variables will be described in terms of effective, average, standard deviation and confidence interval at 95 % of the average, median, range and interquartile range. The qualitative variables will be described in terms of effective, percentage and confidence interval at 95 % according to exact binomial law. The risks of first occurrence of events will be estimated by the non-parametric method of Kaplan-Meier and compared with the Log-Rank test. A model of proportional risks from Cox will be used in order to take adjustments into account if necessary. The log-linear and risk proportionality hypotheses will be systematically verified.

For qualitative data, in each country, the interviews, focus groups and verbal interactions during MDT meetings (“real” and “theoretical”) will be submitted for thematic categorical content analyses (with the help of the NVivo9 software). This will allow for updating the principal obstacles and facilitators of operatory decisions in the framework of MDT meetings of patients with PRC-bTME and LRRC.

The concordance on the indication to the resectability between France and Australia will be estimated by the Kappa coefficient of Cohen. The confidence interval of 95 % of this estimation will be calculated by Fisher’s exact method based on distribution.

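### The 95% confidence interval for Cohen's kappa is assigned to a Fisher exact method, which is not an interval method for kappa; the size and direction of the resulting error depend on what was meant

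*Protocol article*

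**What the plan says.** In the Statistical analysis section, agreement between the two countries on the indication for resection "will be estimated by the Kappa coefficient of Cohen". The next sentence says that the 95% confidence interval "of this estimation will be calculated by Fisher’s exact method based on distribution". The distribution is not named, nor is the quantity to which the method is applied.

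Earlier in the same section, categorical variables are given a separate rule: "percentage and confidence interval at 95 % according to exact binomial law".

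The sample-size section gives kappa its own target: "Kappa coefficient of 0.6, and show that this is different from 0.4", "with a power of 80 % and an alpha risk of 5"%. It concludes: "The necessary number of patients to include is 240". It does not state what share of tumours each country's readers are expected to judge resectable.

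**The concern.** Cohen's kappa is κ = (po − pe)/(1 − pe), where po is the observed agreement and pe is the chance agreement estimated from both readers' margins. It is not a count out of n, and its variance depends on the margins.

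The phrase in the article has two usual meanings. Fisher's exact test addresses independence in a 2×2 table (κ = 0) and returns a p-value, with no interval for kappa. The exact interval computed from the F (equivalently beta or binomial) distribution is for one proportion. Neither is a confidence interval for kappa.

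The interval matters because the sample-size section sets out to show that kappa differs from 0.4, and the analysis section names no other inferential procedure for kappa. If the interval does not have its nominal coverage, a comparison with 0.4 based on it does not have its nominal 5% error.

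**Working it through.** **Inputs from the article.** Expected kappa 0.6, comparison value 0.4, power 80%, alpha 5% (read as two-sided), n = 240.

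**Assumption.** The proportion that each reader judges resectable is not given. I take equal margins of 10% to 50%. The only rates in the article are the clinical resection rates for the primary endpoint ("in France the clinical resection rate will be 20 % and that in Australia it will be 40"%). These are not reader margins. With margins of 20% and 40%, kappa could not reach 0.6 in any case: the largest po is 0.80 and pe = 0.08 + 0.48 = 0.56, so the maximum is 0.24/0.44 = 0.545.

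**Step 1: large-sample variance of kappa (Fleiss-Cohen-Everitt).**

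n·Var = (A + B − C)/(1 − pe)², where
- A = Σ pii[1 − (pi. + p.i)(1 − κ)]²
- B = (1 − κ)² Σ(i≠j) pij(p.i + pj.)²
- C = [κ − pe(1 − κ)]²

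At 20% margins and κ = 0.6:
- pe = 0.04 + 0.64 = 0.68, and po = 0.68 + 0.6 × 0.32 = 0.872.
- The cells are 0.136, 0.064, 0.064 and 0.736.
- A = 0.136 × 0.84² + 0.736 × 0.36² = 0.1913.
- B = 0.16 × 0.128 = 0.0205.
- C = (0.6 − 0.272)² = 0.1076.
- n·Var = 0.1042/0.1024 = 1.018, so sd = 1.009 and SE = 1.009/√240 = 0.0651.

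**Step 2: reproduce the planned 240.** N = [(1.96·sd0 + 0.842·sd1)/0.2]². At 20% margins sd0 (κ = 0.4) = 1.128 and sd1 (κ = 0.6) = 1.009. This gives N = (3.06/0.2)² ≈ 235, and a goodness-of-fit kappa formula gives 241. The stated 240 is therefore reproduced by a proper kappa method at an assumed 20% margin. Other margins give 411 (10%), 181 (30%) and 153 (50%).

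**Step 3: reading (a), kappa treated as a binomial proportion.** With 0.6 × 240 = 144, the exact (Clopper-Pearson) limits are 0.535 to 0.662, a width of 0.127. Coverage comes from 20,000 simulated tables per scenario.

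| Margin, both readers | Large-sample kappa CI (width) | Width ratio, reading (a) | Coverage of (a) at κ = 0.6 | (a) excludes 0.4 when κ = 0.4 |
|---|---|---|---|---|
| 10% | 0.429–0.771 (0.343) | 0.37 | 54% | 50% |
| 20% | 0.472–0.728 (0.255) | 0.50 | 68% | 38% |
| 30% | 0.489–0.711 (0.222) | 0.57 | 75% | 33% |
| 50% | 0.499–0.701 (0.202) | 0.63 | 78% | 28% |

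The large-sample kappa interval covered about 94% to 95% at κ = 0.6 and wrongly excluded 0.4 in about 5% to 7% of tables at κ = 0.4.

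**Step 4: reading (b), exact limits for raw agreement, rescaled.** At 20% margins the exact interval for po = 0.872 is 0.823 to 0.912. Applying (po − pe)/(1 − pe) with pe = 0.68 held fixed gives 0.447 to 0.723. The width is 0.277, which is 1.08 times the large-sample width. Over 10% to 50% margins the ratio is 1.13 down to 1.04 and coverage is about 96% to 98%. If the agreement limits were left unscaled, they would not be limits for kappa: 0.823 to 0.912 does not even contain 0.6.

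**Step 5: reading (c), Fisher's exact test.** This yields no interval for kappa.

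**The case against.** The fairest defence is that the sentence looks incomplete. A word seems to be missing before its last noun, possibly F, perhaps through translation or text conversion. The authors state the exact binomial rule for percentages separately and name the kappa interval differently, which weakens the idea that they meant to treat kappa as a percentage. A reader might infer from reading (a) that the planned interval is simply half as wide as it should be. The article does not support that: the figure of 0.50 needs both that reading and a 20% margin the article never states, and reading (b) errs in the opposite direction.

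A reader might also infer that the planned conclusion about 0.4 would be false. At the design value of 0.6 that does not follow, because the large-sample interval excludes 0.4 at every margin examined (lower limits 0.429 to 0.499). The conclusion could differ only at lower observed kappas. In addition, the analysis section presents the interval as part of estimation and does not say that it will serve as the test of 0.4.

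These points limit the size and certainty of the consequence. They do not rescue the sentence: none of the readings examined is a standard interval for kappa. The method is also stated outright, so this is not a detail left to an analysis plan that is not shown.

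**Conclusion.** The point holds as a wrongly specified method. The article assigns the kappa interval to a procedure that does not produce one, and its wording does not show what would actually be computed.

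The size is conditional. If kappa is entered as a proportion, the interval is 0.37 to 0.63 of the proper width and covers 54% to 78%, and 0.4 is wrongly excluded in 28% to 50% of studies with true kappa 0.4. If raw agreement is rescaled, the interval is 4% to 13% too wide. These figures rest on n = 240, kappa 0.6 (0.4 for the false exclusions) and assumed equal margins of 10% to 50%. Neither the direction nor the amount of error can be fixed from the text.

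The matter concerns one secondary endpoint. The kappa point estimate, the primary comparison of resection rates and the 240 patients are unaffected. It should be corrected before analysis, but it does not threaten the trial's main result.

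**What to change.** Replace the sentence on the kappa interval with one stating that the 95% confidence interval will use the large-sample (Fleiss-Cohen-Everitt) variance, as given by SAS PROC FREQ with the AGREE option. Add that the comparison with 0.4 in the sample-size section will be tested with a matching kappa variance. Keep exact binomial intervals for raw proportions, including raw percentage agreement.

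The cost is one or two sentences. SAS is already the named software, and neither new data nor a new sample size is needed. The reported interval may be wider than the one the authors had in mind.
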